## Abstract

In modern society, physical activity is essential for maintaining both physical and mental health, particularly as technological advancements have contributed to a sedentary lifestyle. The World Health Organization recommends a minimum of 150 minutes of moderate exercise weekly for adults; however, many individuals, especially those with knee osteoarthritis (KOA), do not meet these guidelines. KOA, the most common form of arthritis, affects millions globally and leads to significant disability, pain, and reduced quality of life. The condition is exacerbated by sedentary behavior and high body mass index (BMI). Educational interventions promoting lifestyle changes, including increased physical activity, have shown effectiveness in managing KOA. To address the low adherence rates to physical activity guidelines among KOA patients, the “Move for Knee”™ mobile app was developed. This app offers personalized exercise programs based on user-input data about lifestyle and activity levels, aiming to enhance patient engagement and adherence. Its features include exercise tracking, real-time monitoring, and communication with healthcare providers through an integrated chat function. A randomized controlled trial (RCT) will evaluate the app's efficacy in improving pain, function, and quality of life among individuals aged 45–70 with KOA. The study will compare outcomes from users of the app against a control group receiving standard advice on physical activity. Preliminary expectations suggest that the app will improve adherence to exercise recommendations and overall management of KOA, while also providing cost-effective healthcare solutions. The ultimate goal is to empower patients, enhance their self-management capabilities, and improve their overall health outcomes through an innovative, technology-driven approach. Future research will focus on assessing the app's clinical effectiveness and usability across various patient demographics.

## Introduction

1

Physical activity, in modern society, is key to ensure physical and mental well-being, preventing disabling chronic conditions, and improving overall health and quality of life (1).

The evolution of society, particularly advancements in technology, has progressively reduced the amount of physical activity and daily energy expenditure, with significant negative effects on global health (2).

The World Health Organization (WHO) recommends at least 150 minutes of moderate physical activity per week for adults. However, many individuals fail to meet even this minimum threshold. Lack of exercise is considered a significant risk factor for many conditions, including obesity, type 2 diabetes, cardiovascular diseases, hypertension, and degenerative joint disorders, particularly knee osteoarthritis (3).

Knee osteoarthritis (KOA) is the most prevalent type of arthritis and a highly disabling condition (4). In 2023, approximately 364.58 million prevalent cases of KOA were recorded worldwide, with 29.51 million incident cases, and 11.53 million disability-adjusted life years (5, 6) attributed to the disease. Patients with KOA commonly experience knee pain, limited morning stiffness, reduced functionality, progressive decline of activities of daily living (ADL), decreased quality of life, and significant healthcare resource utilization (7, 8). Both constitutional and mechanical factors contribute to the onset and progression of this degenerative joint disease, such as high body mass index (BMI) or sedentary behavior. Among the recommended interventions for KOA, educational and lifestyle advice, including weight management and physical activity, represent an effective therapeutic strategy to improve clinical condition and functional outcomes (9, 10). Despite these recommendations, less than 20% of men and fewer than 10% of women with KOA adhere to the prescribed physical activity guidelines (11).

To improve adherence to physical activity in people with KOA, a personalized approach has been suggested. This approach involves customizing physical activity goals, monitoring progress in real-time, creating a sustainable environment, and fostering a supportive social network to promote an active lifestyle (12). These measures could encourage patients to engage in higher levels of physical activity. In this context, digital health technologies have proven to be as effective as traditional treatments in patient education, physical activity promotion, and exercise interventions while also being cost-effective for the KOA population.

The aim of this study is to develop and implement a mobile app, “Move for Knee”™, featuring specific physical activity programs designed for Italian individuals with KOA. Furthermore, this paper describes the study protocol of the RCT designed to investigate the efficacy of the clinical application of app for managing KOA.

## Materials and methods

2

### The “Move your Knee”™ app

2.1

The mobile APP called “Move Your Knee”™ is divided into four main sections:
1)Know Your Knee: this section collects patient-entered data to help understand their lifestyle habits, daily physical activity levels, and information related to KOA. The data related to the symptoms experienced by patients and their intensity are reported through a questionnaire based on selected categories from the International Classification of Functioning, Disability, and Health (ICF) brief core set related to osteoarthritis (OA) (Table 1). Finally, the individual's level of physical activity is self-assessed using the International Physical Activity Questionnaire (IPAQ).

**Table 1 T1:** Categories belong to the brief ICF core Set for osteoarthritis-OA (in red those specific to lower limb OA).

Categories of the component “body functions”:
ICF code ICF category title
2nd level
b280 sensation of pain
b710 mobility of joint functions
b730 muscle power functions
Categories of the component “body structures”:
ICF code ICF category title
s730 structure of upper extremity
s750 structure of lower extremity
s770 additional musculoskeletal structures related to movement
Categories of the component “activities and participation”:
ICF code ICF category title
d445 hand and arm use
d450 walking
d540 dressing

At the end of the questionnaire, the app's integrated algorithm calculates the patient's estimated level of physical activity. Based on this, the app assigns a specific exercise program, including detailed execution parameters (e.g., weekly frequency) and advice for safely performing the exercises to achieve specific functional goals.

The exercises available are selected according to national and international recommendations and guidelines for KOA (13, 14). As suggested by the app, it is important for patients to consider their symptom severity before starting the exercise.
2)Move Your Knee: in this section, patients can select the difficulty/intensity level for their exercises. Advanced levels are locked until earlier objectives are achieved.The app offers five levels, each represented by an evocative image reflecting the functional progression and user type: *Hawk, Tiger, Bull, Turtle, Sloth*.

Once an exercise program is initiated, the app provides detailed instructions for each exercise, including duration, sets and repetitions. Using a motion capture function, patients uses device's camera to record their exercises to ensure proper and safe execution. This feature enables users to perform exercises and share their execution with the doctor to monitor whether they are being done correctly and safely. The captured data is securely stored within the app and can be shared with healthcare providers through the chat feature, allowing them to provide tailored feedback and adjust exercise programs as needed.
3)Step by step: this section allows patients to track and monitor their daily progress, providing a real-time overview of their achievements.4)Chat: to facilitate direct communication with the doctor, the app includes a native instant messaging service. Patients can contact their doctor by communicating, share files, and upload videos for better monitoring and feedback.The system is complemented by a control panel designed for doctors, accessible via a terminal or PC. The control panel provides the following functionalities:
1)patient registration on a dedicated web platform;2)access to patient files linked to the referring doctor;3)monitoring of patient progress to ensure adherence to the program;4)access to chat feature for direct communication.Figures 1–4 provide a detailed visual description of the app and the control panel.

**Figure 1 F1:**
[figure not shown]
Visual overview of the “move for knee”™ app.

**Figure 2 F2:**
[figure not shown]
Visual overview of the medical website page linked to the app.

**Figure 3 F3:**
[figure not shown]
Levels of physical activity proposed.

**Figure 4 F4:**
[figure not shown]
Details of the medical chat feature within the “move for knee”™ app.

### Study protocol description

2.2

#### Participants

2.2.1

This no-profit, interventional, double-arm, monocentric study, will include men and women aged 45–70 years with unilateral or bilateral tibiofemoral KOA, diagnosed according to the American College of Rheumatology criteria for KOA, and radiographic findings (Kellgren-Lawrence grade 1–3).

Potential participants will be referred to the Physical Medicine and Rehabilitation Unit at the University of Campania “Luigi Vanvitelli.” Referrals may come from general practitioners, orthopedic specialists, or rheumatologists who identify eligible candidates based on the inclusion criteria. All participants will be required to provide informed consent before enrollment in the study, ensuring they understand the study's purpose, procedures, potential risks, and benefits. The study will adhere to good scientific and clinical practices as outlined in the Declaration of Helsinki. The Ethical Committee of the University of Campania “Luigi Vanvitelli” (Committee's reference number: Prot. 0008758/i-21/03/2024) has approved the study. The study protocol has been registered in ClinicalTrial.gov (NCT06721208).

Inclusion and exclusion criteria are reported in Table 2.

**Table 2 T2:** Inclusion and exclusion criteria.

Inclusion criteria
• Patients with unilateral or bilateral tibiofemoral osteoarthritis according to the American College of Rheumatology classification criteria for osteoarthritis, aged between 45 and 70 years, with radiographic findings (Kellgren-Lawrence grade 1–3)
• Expression of consent to participate in the study through a signed informed consent form
• Ability to understand and use the APP through a practical demonstration in an outpatient setting
Exclusion criteria
• Psychiatric disorders that could potentially invalidate informed consent
• Pregnancy or breastfeeding

#### Intervention

2.2.2

The study is designed as a double-arm interventional trial, indicating that participants will be divided into two groups for comparison:
-patients who will use the “Move for Knee” APP (intervention arm);-patients who will be advised to engage in unsupervised physical activity (control arm).Participants who meet the inclusion criteria and provide informed consent will be randomly assigned to one of the two intervention groups. The randomization process will be performed using a consecutive 1:1 allocation ratio (intervention:control) and it may involve the use of computer-generated random numbers or a randomization table to ensure unbiased assignment.

#### Outcome

2.2.3

The following primary outcome measures will be conducted:
•Multidimensional pain evaluation to evaluate qualitative and quantitative aspects of pain:
○Brief Pain Inventory (BPI), including severity and interference indices (BPI-SI, BPI-II).○Leeds Assessment of Neuropathic Symptoms and Signs (LANSS) scale for the neuropathic pain component.•Stiffness and function to measure improvements in mobility and daily activities:
○Western Ontario and McMaster Universities Osteoarthritis Index (WOMAC).As secondary outocome measure it will be performed:
•Quality of life assessment through:
○EUROQoL-5 Dimension (EQ-5D), to evaluate overall well-being and health statusOutcome measures will be collected at baseline and at specified intervals throughout the study, such as at 30 (T1), 90 (T2), and 180 days (T3) post-enrollment, to assess both short-term and long-term effects of the interventions.

For patients in the intervention group, user experience and adverse effects of the app will be evaluated using an open-ended question: “*Describe your experience with the app.*” This feedback will be collected at T1, T2, and T3.

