Finally, when comparing the development processes of the Move Your Knee app with other existing apps, such as the Knee Osteo-Arthritis Lifestyle App (iKOALA), it is evident that the KOALA App was developed in two phases: planning (which included literature review and qualitative data collection) and optimization (involving user trials and feedback) (22).

The KOALA app emphasizes a person-based approach (PBA) to development, ensuring that user needs and barriers are central to the design process. Moreover, it provides comprehensive lifestyle management, including guidance on physical activity, education, and social support.

In contrast, the Move Your Knee app focuses on delivering personalized exercise programs based on self-reported data, integrating real-time tracking and feedback mechanisms. It also incorporates self-assessment tools and exercise programs grounded in MET, featuring a motion capture function that allows users to record their exercises, thereby facilitating remote monitoring by healthcare providers.

Another significant difference lies in the study design and outcome measures. The KOALA app emphasizes iterative development and continuous user engagement throughout the process, focusing on qualitative user experience and usability evaluation during the development phase. It plans to conduct randomized controlled trials to validate the app in real-world settings after making revisions based on user feedback.

Conversely, the Move Your Knee app aims to conduct a double-arm interventional trial that compares the app's effectiveness against a control group receiving standard advice for physical activity. It structures a precise and concise protocol according to quantitative outcome measures assessed at multiple time points (30, 90, and 180 days) to evaluate pain, stiffness, function, and quality of life. Additionally, it employs a structured feedback mechanism for the intervention group to gather insights on user experience and any adverse effects. The Move Your Knee app also sets defined inclusion criteria, targeting men and women aged 45–70 years with unilateral or bilateral tibiofemoral KOA diagnosed according to established criteria.

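### Adverse effects are described for the app arm only, through one question that does not mention harm, so the plan gives no between-arm comparison of discrete adverse events

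*Protocol article*

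**What the plan says.** The methods text on adverse effects is in the Outcome section (2.2.3) of the protocol article: "For patients in the intervention group, user experience and adverse effects of the app will be evaluated using an open-ended question". The article then gives the exact wording, "Describe your experience with the app", and the timing: "This feedback will be collected at T1, T2, and T3". These time points are given as "such as at 30 (T1), 90 (T2), and 180 days (T3) post-enrollment".

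The Discussion (section 4) describes the same collection again: "it employs a structured feedback mechanism for the intervention group to gather insights on user experience and any adverse effects".

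The Intervention section (2.2.2) defines the comparator as "patients who will be advised to engage in unsupervised physical activity (control arm", with a "consecutive 1:1 allocation ratio (intervention:control" allocation. Nowhere does the article describe adverse-event collection in that arm. Section 2.1 describes what app users receive: "the app assigns a specific exercise program, including detailed execution parameters".

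**The concern.** Two features of the stated method look wrong.

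- **Only one arm is asked.** Knee osteoarthritis brings pain and flares of its own, and control patients are also advised to be active. An event in the app arm can be interpreted only against the rate in the control arm, and no such rate is collected.
- **The question does not ask about harm.** It invites comment on the app. A patient who fell, strained a muscle or had a bad fortnight with the knee, and who does not blame the app, has no reason to mention it.

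At stake is whether the trial can report falls, injuries, flares and care sought by randomised arm, for an intervention in which patients follow an assigned exercise programme. The Discussion also suggests that the app may lead to fewer flare-ups. With the collection described, that suggestion could not be tested by counting flares in the two arms.

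**Working it through.** The article gives no sample size, power or adverse-event rate, and the point needs none. The check is to set the statements side by side and see which comparisons they allow.

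**1. What is collected, and from whom**

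| Item | App arm | Control arm |
|---|---|---|
| Open-ended question at T1, T2, T3 (Outcome) | Yes | Not described |
| Feedback on adverse effects (Discussion) | Yes | Not described |
| Chat channel to the doctor (section 2.1) | Yes, part of the app | Not described |
| BPI, LANSS, WOMAC, EQ-5D (Outcome) | Yes | Yes; no arm restriction stated |

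**2. Discrete events**

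The between-arm contrast is the risk difference

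RD = x_A / n_A − x_C / n_C,

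where x is the number of patients with an event, n the number randomised, A the app arm and C the control arm. The described plan supplies a version of x_A and no x_C. RD therefore cannot be estimated for any n_A and n_C.

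The app-arm count is incomplete as well. If a proportion s of patients with an event mention it when asked about the app, the recorded count is about s × x_A. The article gives nothing from which to set s. Because the prompt names neither harm nor any kind of event, s is probably below 1, so the recorded count is probably too low.

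Spontaneous reports do not fill the gap. The chat gives app users a route to report problems that is not described for controls, so unprompted reports would also be unequal between arms.

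**3. What the symptom scales can and cannot cover**

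BPI, LANSS, WOMAC and EQ-5D are listed for the trial at baseline, 30, 90 and 180 days. A mean worsening in one arm can be compared with the other. The scales do not count falls, injuries or care sought. They can also miss a flare that starts and settles between assessments: the gap is 90 − 30 = 60 days from T1 to T2, and 180 − 90 = 90 days from T2 to T3.

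**4. The two descriptions of the same item**

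The Outcome section describes a single open-ended question; the Discussion calls the mechanism structured. A fixed question at fixed times could loosely carry that label, so this is an editorial mismatch and adds no weight to the point.

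**The case against.** The strongest objection is that the Outcome section restricts effects *of the app*, which only app users can have, and says nothing against routine event recording in everyone. The article condenses a protocol described as ethics-approved and registered, and general adverse-event recording is commonly left to the full document.

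Part of this stands. A reader might infer that control-arm events go unrecorded anywhere in the trial. The article does not say that, and a full protocol that records them cannot be excluded. What does not stand is that this is merely an omitted detail. The article fixes the arm, the instrument, the wording and the timing, and states the one-arm restriction twice. Nor does limiting the question to effects of the app solve the problem: it leaves patients to judge causation, which the randomised comparison exists to settle.

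A second objection is that the symptom scales are themselves safety information. This stands in full. A reader might infer that the trial will yield no between-arm safety information at all; the unrestricted scales at four time points contradict that.

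A third is that the stated aim is efficacy on pain, function and quality of life, with no between-arm safety objective, and that the exercises are drawn from guidelines. This stands as a limit on severity: no planned efficacy conclusion fails. It does not make the stated method adequate for evaluating adverse effects, which is the purpose the article gives it.

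**Conclusion.** The point holds for discrete adverse events. As described, the plan provides no between-arm comparison of falls, injuries, care sought or flares that resolve between assessments, and it probably under-counts them in the app arm. The size is qualitative: the contrast cannot be estimated at any sample size. The document gives no event or reporting rates, so no numerical size is put on the under-count.

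The conclusion does not extend to average worsening of pain, stiffness, function or quality of life, which BPI, LANSS, WOMAC and EQ-5D can compare between arms. The efficacy outcomes are unaffected, so this is a worthwhile and cheap improvement, not a defect that undermines the trial's main inference.

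It rests on one assumption, that the article describes event collection as it will be done. If the full protocol records events in both arms, the defect lies in the article's description and only that needs correcting.

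**What to change.** - At T1, T2 and T3, put the same explicit adverse-event question, or the same short solicited list, to both arms. Word it without reference to the app.
- Report event counts and risk differences by randomised arm.
- Keep the existing open-ended question for the app arm, as user-experience feedback only, and stop describing it as the evaluation of adverse effects.
- Bring the Outcome section and the Discussion into line, including the word structured.
- If the full protocol already records events in both arms, correct both sections to say so.

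The cost is one short form at assessments already planned, and a minor amendment. The downside is that more events will be recorded in both arms. The change should be made before follow-up data accrue, because events not asked about in controls at the time cannot be reliably recovered later.

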## Results

3

The development of the “Move Your Knee”™ mobile app aims to improve the management of KOA by providing an innovative approach to engage patients in self-management and encourage adherence to recommended physical activity. This project seeks to help individuals affected by KOA to adopt a healthier lifestyle by increasing their physical activity habits, through an easy-to-use mobile app. The “Know your Knee” section of the app collects patient data, empowering individuals with KOA to take an active role in their healthcare decisions, via a patient-centered approach. Since people with KOA often lead sedentary lifestyles and may lack adequate information about the appropriate levels of physical activity needed to safely improve their mobility and independence, the expected outcomes of this initiative are designed to address these gaps. The experimental study is expected to demonstrate high levels of adherence to and usability of the app, largely due to the training provided by physical therapists. The app will also deliver weekly feedback on physical activity performed, enhancing user engagement. To encourage compliance, users will be associated with a visual representation that corresponds to their activity level (e.g., “Hawk,” “Tiger,” “Bull,” “Turtle,” “Sloth”). Additionally, the app includes a chat function that provides a direct link to healthcare professionals, functioning as an “e-referral” system and enhancing user experience and satisfaction. Ultimately, the routine use of this app is expected to produce measurable health benefits for patients, offering a favorable cost-to-benefit ratio compared to alternative treatments.

